## Abstract

**Background:**

Multiple sclerosis (MS) is a chronic condition of the central nervous system, affecting around 1 in every 600 people in the UK, with 130 new diagnoses every week. Cognitive difficulties are common amongst people with MS, with up to 70% experiencing deficits in higher-level brain functions—such as planning and problem-solving, attention, and memory. Cognitive deficits make it difficult for people with MS to complete everyday tasks and limit their abilities to work, socialise, and live independently. There is a clear need—and recognised research priority—for treatments that can improve cognitive functioning in people with MS. The absence of effective cognitive interventions exacerbates burdens on the services accessed by people with MS—requiring these services to manage sequelae of untreated cognitive deficits, including reduced quality of life, greater disability and dependence, and poorer adherence to disease-modifying treatments. Our planned research will fill the evidence gap through developing—and examining the feasibility of trialling—a novel online cognitive rehabilitation programme for people with MS (SMART). The SMART programme directly trains relational skills (the ability to flexibly relate concepts to one another) based on theory that these skills are critical to broader cognitive functioning.

**Methods:**

The primary objective of this study aims to conduct a feasibility study to inform the development of a definitive trial of SMART for improving cognitive functioning in people with MS. The secondary objective is to develop the framework for a cost-effectiveness analysis alongside a definitive trial, and the exploratory objective is to assess the signal of efficacy.

**Discussion:**

As a feasibility trial, outcomes are unlikely to immediately effect changes to NHS practice. However, this is a necessary step towards developing a definitive trial—and will give us a signal of efficacy, a prerequisite for progression to a definitive trial. If found to be clinically and cost-effective, the latter trial could create a step-change in MS cognitive rehabilitation—improving service delivery and optimising support with limited additional resources.

**Trial registration:**

Registration ID: ClnicalTrials.gov: NCT04975685—registered on July 23rd, 2021.

Protocol version: 2.0, 25 November 2021

**Supplementary Information:**

The online version contains supplementary material available at 10.1186/s40814-022-01152-7.

## Background

Multiple sclerosis (MS) is a chronic condition of the central nervous system, affecting around 1 in every 600 people in the UK, with 130 new diagnoses every week [1]. Common symptoms of MS include limb weakness, fatigue, and pain. These symptoms typically come in waves (as ‘attacks’)—lasting weeks before remitting—but often, over time, become permanent, leading to increased disability and physical decline.

Cognitive difficulties are common amongst people with MS, with up to 70% experiencing deficits in higher-level brain functions [2]—such as planning and problem-solving, attention, and memory. In a national survey, these cognitive difficulties were identified as the most debilitating and distressing consequence of MS [3]. Cognitive deficits make it difficult for people with MS to complete everyday tasks and limit their abilities to work, socialise, and live independently [4]—abilities integral to wellbeing [5]. Natural history studies of cognitive dysfunction in MS indicate that deficits are unlikely to improve and often worsen [6]—with great costs to people with MS, their families, and society [7].

There is a clear need—and recognised research priority—for treatments that can improve cognitive functioning in people with MS [8]. Whilst there has been progress in diagnosing cognitive difficulties, efficacious treatment options remain elusive [9, 10]. However, one of the more promising treatment pipelines is cognitive rehabilitation [11]—a structured set of activities to retrain cognitive skills or to improve coping with cognitive deficits in daily life. Whilst several reviews have found some positive effects of cognitive rehabilitation in people with MS, these are based on poor quality randomised controlled trials (RCTs) [12, 13]. More recent, robustly-designed studies, however, are encouraging [9, 14]and suggest that cognitive retraining can be effective for focal deficits (e.g. intensive attentional training for attentional deficits), but questions remain as to the breadth, practical importance, reproducibility, and real-world scalability of such interventions.

Studies to date have typically not been predicated on a clear theoretical rationale for intervention, nor sought to examine possible mechanisms of change. This is problematic as, in the absence of a theoretical framework or process-based examination, it is difficult to synthesise across studies and understand or optimise intervention effects. Currently, no evidence-based recommendations exist for either practice standards, guidelines, or options in MS rehabilitation [14]—reflecting the absence of any ‘gold standard’ intervention(s) and a need to identify approaches more apt to address the cognitive needs of MS patients [15].

Thus, the problem to be addressed is the lack of treatment options for cognitive difficulties in people with MS. Our planned research will fill the evidence gap through examining the feasibility of trialling a novel online cognitive rehabilitation programme for people with MS. Our approach to cognitive rehabilitation is distinctive from previous interventions (e.g. [16]) in three key respects. Specifically, our approach:Is theory-based, whereas other interventions collate various techniques into a single atheoretical packageEmploys a focussed, low-intensity cognitive intervention (targeting direct improvement and restoration of cognitive functioning), whereas other interventions include cognitive rehabilitation as part of a broader package (of physical and occupational therapy) complicating future understanding of mechanisms of effect and cost-effectivenessWill train a focal ability, but test for external validity (i.e. whether training transfers to everyday cognition and behaviour), whereas other interventions typically ‘train to test’ (i.e. involve practising final performance assessments, with questionable generalisability beyond this). This latter distinction is important, as meta-analysis has shown that extant cognitive training programmes show weak transferability (i.e. do not generalise beyond train-to-test effects [17]); theoretically, our focal intervention could produce both near- and far-transfer of effects, across indices of cognitive functioning. This was also highlighted as important by our PPI group.

These features also distinguish our (online training) intervention from commercial ‘brain training’ packages (e.g. Lumosity) and other mentally stimulating leisure activities for which the evidence is equivocal at best [18, 19]. Our intervention—*Strengthening Mental Abilities Through Relational Training* (SMART) [20]—is a web-based cognitive training programme that directly trains ‘relational skills’—the skills necessary to understand how concepts relate to one another. SMART is grounded in behavioural science, specifically Relational Frame Theory, which proposes that all human language and complex cognition are underpinned by these relational abilities—such that improving them should enable more rapid and efficient thinking and learning. This proposition from behavioural science is convergent with evidence from education, cognitive science, linguistics, and neuroscience, suggesting that successful cognition involves the ability to relate symbols for functional purposes [21]. Relational skills are developed over time (from infancy) as individuals interact with their environment [22]– and scaffold cognitive abilities such as language, problem-solving, and deductive reasoning [20, 23]. By targeting conceptually and empirically supported core constituents of cognition, SMART can potentially facilitate improved functioning across multiple cognitive domains [20].

In several pilot studies, SMART has shown promise for improving a range of cognitive skills in children [24]. A recent meta-analysis found a moderate effect of SMART on measures of nonverbal intelligence, supporting far-transfer of training, although the primary studies were observed to be at high risk of bias [25]. Whilst most research to date has focussed on increasing scholastic aptitude and general cognitive ability with children, a recent pilot RCT investigated SMART and Treatment-As-Usual (TAU) versus TAU alone (where TAU is pharmacological) for people with Alzheimer’s dementia [26]. Significant small improvements in cognitive abilities were reported for the SMART group at 3-month follow-up. Presti et al. [26] have made the initial steps of transposing SMART into a clinical setting to improve cognitive outcomes for those with deficits and who are in decline, and their results indicate that the programme could be feasibly adapted for use in clinical domains. However, to date, the SMART programme has not undergone rigorous clinical trial evaluation.

In response to the current state of evidence, our work will examine the feasibility of trialling the SMART programme for people with MS. An online programme designed to train relational skills and potentially improve cognitive function may be a cost-effective, accessible intervention for people with MS—addressing unmet patient need for effective cognitive rehabilitation. The theoretical basis of SMART offers advantages over other past-and-ongoing trials and enables us to pursue development in accordance with Medical Research Council (MRC) guidelines for developing complex interventions [27].

### Objective

Primarily, we aim to conduct a feasibility study to inform the development of a definitive trial of SMART for improving cognitive functioning in people with MS. Specifically, we will assess:Acceptability and feasibility of the intervention, delivery format, inclusion/exclusion criteria, baseline and outcome measures, randomisation protocol, and study proceduresParticipant recruitment and retention ratesSample size needed for fully powered trial

Our secondary objective is to develop the framework for a cost-effectiveness analysis alongside a definitive trial. Our exploratory objective is to assess the signal of efficacy.

## Methods

### Trial design

A three-arm feasibility RCT comparing (1) SMART + treatment-as-usual (TAU) with (2) TAU and (3) active control (‘sham’) training + TAU. We decided on three arms because this will be most informative for the envisaged definitive trial design: It is crucial to include both passive and active control conditions in definitive trials of cognitive rehabilitation, in order to detect any effects over-and-above training-unspecific effects (e.g. [28]. We decided against using a waitlist control because of evidence that waiting-list allocation can have negative effects (e.g. reducing self-management efforts over the waiting period) [29]; moreover, the ethical imperative for providing SMART to all participants is unclear given the as-yet-unknown acceptability and efficacy of this experimental intervention.

### Setting

The study will be set in two hospital-based neurology outpatient clinics for people with MS: in Nottinghamshire, UK (site information available from the corresponding author).

### Eligibility criteria

#### Inclusion criteria

Diagnosis of MS received ≥3 months pre-enrolment (allowing for acute adjustment, as per other trials of cognitive rehabilitation, e.g. CRAMMS [16])Age 18-89 (to meet the standardisation criteria of psychometric assessments)Cognitive difficulties as assessed by Perceived Deficits Questionnaire (PDQ) self-report (≥27) and Symbol Digit Modalities Test (SDMT) performance (1.5 SDs or more below the normative reference value)Able to read and speak English to the standard necessary for completing assessment and intervention proceduresAble and willing to access a computer/tablet/smartphone with an internet connection throughout the studyAble and willing to give informed consent

#### Exclusion criteria

Currently receiving cognitive rehabilitationPreviously received SMART trainingVision or hearing problems precluding completion of procedures

### Interventions

#### TAU

Participants in this arm will receive treatment-as-usual (TAU). Content of TAU for cognitive concerns, based on our clinical experience and knowledge, is often informational support from an MS Nurse with signposting to the MS Society/MS Trust websites.

#### SMART + TAU

Participants in this arm will receive treatment-as-usual (TAU) plus the experimental SMART intervention (theory-based cognitive training).

The standard SMART programme will be adapted for intervention [20]—augmenting the standard self-directed programme through facilitator support and the provision of supplementary, accessible guidance materials (based on usability testing with MS patients) [30]. The programme involves presenting a series of logical reasoning problems, with corrective feedback after every response, in the course of training users to derive comparative relationships amongst novel stimuli (‘nonsense words’). The complexity of the problem-solving tasks increases in a stepwise manner over 70 stages of training, requiring increasing relational abilities to progress. Novel stimuli and task configurations are used on every trial, in order to enhance far transfer (i.e. there is no single ‘set’ of correct answers to a single set of specific problem-solving tasks). Figure 1 provides examples of SMART training trials of varying complexity. Please see Additional file 1 for the Template for Intervention Description and Replication (TIDieR) checklist [31] which has been used to describe the intervention to facilitate replication of the intervention in the future, showing the different aspects that are required of an intervention (i.e. who delivers the intervention, how often, when and where).

**Fig. 1 Fig1:**
[figure not shown]
Examples of SMART training tasks of varying complexity

Participants are typically encouraged to complete the SMART intervention for 30min per session, for a total of 1.5hours per week. However, SMART is incremental and can be completed at the participant’s own pace. Each stage includes a training and a test phase. During training, the participant is required to respond correctly to 16 consecutive exemplar tasks for that stage, within a time limit (typically 30 s per exemplar, to ensure fluency). Tasks continue until this criterion is reached, with corrective audio-visual feedback (‘correct’ or ‘wrong’) provided after each response. Mastery of training is confirmed by performance in a test phase: wherein the learner must respond correctly to a single finite block of 16 consecutive exemplar tasks without feedback. If they pass, they move onto the next stage. If they do not pass, they are directed to repeat both the training and test phase for that stage. It is expected that it would take approximately 12 weeks to complete all 70 stages of the intervention. However, participants will not be required to complete a specific number of stages. Improved cognitive performance has been shown for participants completing just 15 stages (on average) with no clear linear relationship between training completion and outcomes [18].

The intervention will be accessible to participants via their personal computer, tablet, or smartphone with an internet connection. A resource guide prepared for this study will be provided: providing technical information on accessing the programme and a description of how to work through each stage, including a visual chart for progress tracking. Additionally, participants will receive telephone support from an Assistant Psychologist to facilitate intervention access and use. Training activity will be automatically logged for monitoring.

#### Active control (‘sham’) training + TAU

Participants in this arm will receive treatment-as-usual (TAU) plus a control (sham) cognitive training intervention: Sudoku. We selected Sudoku to control for expectancy effects based on popular conceptions that it broadly improves cognitive functions [19, 32], coupled with little evidence supporting this notion [33], and its use as an active control in similar trials [34]. Control training will be delivered online, over the same timeframe/regimen as SMART treatment, and with telephone support to facilitate access—controlling for modality, schedule of engagement, and relational support. To harness expectancy effects [25], we will deliver the control training using a commercial brain training platform—for which there is some published evidence of acceptability and effectiveness in people with MS [35]—where participants will access a study-specific, SMART MS-branded programme. Training activity will be automatically logged.

### Outcomes

#### Primary endpoints

The Primary endpoints in this study relate to the feasibility of proceeding to a Phase III trial. The primary endpoints are based on:Acceptability and feasibility of trial proceduresAppropriateness of eligibility criteria, baseline and outcome measures, audio recording of support sessions, and randomisation protocolRecruitment and retention ratesIntervention acceptability, including progression and completion ratesEstimating the sample size needed for a Phase III RCTCompletion rates of outcome measures

#### Secondary endpoints

The secondary endpoints are related to developing a cost-effectiveness framework for a Phase III trial, based on:Establishing methods for estimating intervention resource use and costsFeasibility of our bespoke service and resource use questionnaireAcceptability of the outcome measures for use in estimating the cost-per-QALY of the intervention

#### Exploratory endpoints

The exploratory endpoints are related to the signal of efficacy and indicative estimation of intervention effects (effect sizes and 95% CIs) for the following outcome measures:

Primary outcome measures for exploratory estimation of effects:Perceived Deficits Questionnaire (PDQ) | Subjective cognitive functioningRepeatable Battery for the Assessment of Neuropsychological Status (RBANS) | Objective cognitive performance (attention, language, visuospatial/constructional abilities, and immediate and delayed memory)Symbol Digit Modalities Test (SDMT) | Objective cognitive performance (processing speed)

Secondary outcome measures for exploratory estimation of effects:Generalized Anxiety Disorder Scale-7 (GAD-7) | AnxietyPatient Health Questionnaire-9 (PHQ-9) | DepressionModified Fatigue Impact Scale–5-Item (MFIS-5) | FatiguePersonal Questionnaire (PQ) | Participant-identified cognitive problemsEQ-5D-5L | Health-related quality of lifeMS Impact Scale–29 (MSIS-29) | MS-specific health-related quality of lifeICECAP-A | Capability wellbeing

### Participant timeline

Table 1 depicts the schedule of enrolment, interventions, and assessments for participants. Over the course of screening and baseline assessment procedures, consenting eligible patients will complete a cognitive assessment battery and questionnaires assessing the impact of living with MS, health-related quality of life, subjective cognitive difficulties, and service/resource use. After completing baseline assessments, participants will be randomly allocated to one of the three intervention arms (using block randomisation with varying block sizes to balance participant numbers across arms). Participants will complete follow-up assessments at 3 and 6 months post-randomisation; after the first follow-up assessment (>3 months post-randomisation) a sub-sample of participants will engage in feasibility-feedback interviews.

**Table 1 Tab1:** Schedule of enrolment, interventions, and assessments

Procedure/assessment	Screen 1	Screen 2	Baseline (0 months)	*Intervention period*	FU1 (3 months)	Interval b/w FUs	FU2 (6 months)
Enrolment:							
Initial eligibility screen	X						
Informed consent	X						
Demographic information	X						
Randomisation			X				
Interventions:							
SMART + TAU				X			
Active control training + TAU				X			
TAU				X			
Assessments:							
PDQ	X				X		X
Symbol Digit Modalities Test (SDMT)		X			X		X
RBANS			X		X		X
Generalized Anxiety Disorder Scale-7 (GAD-7)							
Patient Health Questionnaire-9 (PHQ-9)			X		X		X
Modified Fatigue Impact Scale–5-Item (MFIS-5)			X		X		X
Personal Questionnaire (PQ)			X		X		X
EQ-5D-5L			X		X		X
MS Impact Scale–29 (MSIS-8D; v.2)			X		X		X
ICECAP-A			X		X		X
Service- and resource-use questionnaire			X		X		X
Feedback interviews						X^a^	

*FU* follow-up, *Screen* screening appointment, *ICECAP-A* Investigating Choice Experiments Capability Measure for Adults, *TAU* treatment-as-usual

^a^With selected participants who will be consented prior to the interview

### Sample size

For the purposes of the current study, we will continue to approach and recruit people until we have randomised 60 participants (20 participants per arm). This should provide us with sufficient information in informing the design of a Phase III RCT. Twelve participants per arm would serve to inform trial feasibility outcomes and provide minimally sufficient precision for preliminary parameter estimates [36, 37]. We will recruit 20 per arm because (1) with 20 per arm, our 95% confidence intervals for key estimates (such as trial retention and intervention completion rates) will be narrow enough (<±20%) that, in terms of our criteria for progression to a definitive trial, there will be no substantive misclassification (‘red’ as ‘green’ or vice-versa; please see Table 2) and (2) at least 15 per arm is recommended for estimating variance to inform sample size requirements for a 90% powered main trial aiming to detect effects of moderate (clinically meaningful) magnitude [38]. Given service-activity data and prevalence of cognitive difficulties in people with MS, this target is achievable over a 12-month recruitment phase.

**Table 2 Tab2:** Feasibility assessment

Question	Data	Analysis	Progression criteria
Feasibility of the study	Interviews (i.e. post-trial feasibility interviews)—e.g. acceptability of randomisation; recommended changes to procedures	Framework analysis (structured, purposive coding of qualitative content)	Formative (included to support design of a definitive trial, but no assigned progression criteria cut-offs)
Acceptability of intervention	Drop-out rate (and reasons for withdrawal)	Frequencies/percentages	≥80% of SMART group complete ≥6 sessions (green), 79-60% complete ≥6 sessions (amber), <60% complete ≥6 sessions (red)
	Intervention progression and completion rates	Descriptive statistics/average percentage completion (and range)	Formative
	Interviews	Framework analysis	Formative
*Credibility* of intervention	Interviews (plus relevant comments within session recordings)	Framework analysis	Formative
Feasibility of measures	Missing response-data	Percentage	Formative
	Estimates of completion time	Descriptive statistics	Formative
	Late completion	Percentage	Formative
	Interviews	Framework analysis	Formative
Feasibility of framework for cost-effectiveness analysis	Missing data on intervention resource use	Percentage	Formative
	Missing response data—QALY measures and service and resource use questionnaire	Percentage	Formative
	Estimates of time taken to complete measures - QALY measures and service and resource use questionnaire	Descriptive statistics	Formative
Feasibility of framework for cost-effectiveness analysis (cont…)	Late completion of measures—QALY measures and service and resource use questionnaire	Percentage	Formative
Feasibility of recruitment and randomisation	Numbers of outpatients eligible	Frequencies/percentages	Formative
	Numbers eligible who expressed interest/discussed w/researcher	Frequencies/percentages	Formative
	Numbers consenting/randomised	Frequencies/percentages	≥80% of planned (green), 79–60% of planned (amber), <60% of planned (red)
	Reasons for non-participation? (e.g. online modality as barrier? Unwilling to be randomised?)	Frequencies/percentages	Formative
	Interviews	Framework analysis	Formative
Feasibility of retention within the study	Number completing baseline and outcome assessments at Follow-up 1 (3 months)	Frequencies/percentages	≥80% completing to follow-up 1 (green), 79–-60% completing (amber), <60% completing (red)
Signal of efficacy	Indicative estimation of intervention effects	Estimates of (group-level) effect sizes with 95% CIs and proportions achieving reliable/clinically significant change	Red: 95% CIs exclude the possibility of a meaningful effect size for our screening measures (based on reliable-change criteria)

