### Randomisation and blinding

Participants will be individually randomised at baseline (after consent) in equal proportions to one of three groups (1:1:1 ratio) using block randomisation in permuted blocks of three and six.

Treatment allocation will be computer generated via the electronic trial database in Castor EDC (Castor Electronic Data Capture, available at: https://castoredc.com). Allocation sequence is concealed by Castor EDC until the randomisation of a participant. Castor EDC is used to assign participants to different groups.

Given the nature of the intervention, participants and the intervention-facilitating researchers will not be blinded. No unblinding procedures relating to potential adverse effects are therefore required. The assessments will be conducted by a Research Fellow who will be blind to treatment allocation. We will record any instances of unblinding to assess the feasibility of blinding outcome assessors to allocation.

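### The precision of under ±20% claimed for 20 per arm does not hold for SMART-arm completion rates of 30% to 70%, and the red/green assurance drawn from it depends on an unnamed interval method

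*Protocol article*

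**What the plan says.** The Sample size section plans to recruit "until we have randomised 60 participants (20 participants per arm"). It calls 12 per arm minimally sufficient and gives two reasons for 20. The first is precision: "our 95% confidence intervals for key estimates (such as trial retention and intervention completion rates) will be narrow enough (<±20" per cent), so that "there will be no substantive misclassification (‘red’ as ‘green’ or vice-versa; please see Table 2"). The second is that at least 15 per arm is recommended for estimating variance.

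Table 2 sets the completion criterion as "≥80% of SMART group complete ≥6 sessions (green), 79-60% complete ≥6 sessions (amber), <60% complete ≥6 sessions (red"). Its denominator is the SMART group. The retention criterion uses the same cut-offs, "≥80% completing to follow-up 1 (green), 79–-60% completing (amber), <60% completing (red"), and is not tied to one arm. Allocation is "in equal proportions to one of three groups (1:1:1 ratio"), so the SMART arm has 20 participants and the whole trial 60.

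The section names neither an interval method nor the rate at which the half-width was worked out.

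**The concern.** The half-width of an interval for a proportion depends on the proportion, and at n = 20 it passes 20 points in the middle of the range. The claim carries no such condition, yet it is one of the two reasons for choosing 20 per arm and the only support offered for the red/green statement. That statement matters most where a rating is close, at 16/20 (just green) and 11/20 (just red). If the claim is taken at face value, a just-green completion rating may be read with more assurance than 20 participants give.

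**Working it through.** **Inputs.** n = 20 for SMART completion and n = 60 for pooled retention (Sample size; Randomisation and blinding). Cut-offs of 80% and 60% (Table 2), which at n = 20 mean green at 16 or more, amber at 12 to 15 and red at 11 or fewer. Two-sided 95%, z = 1.96.

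**1. The plan's figure.** Wald half-width = 1.96 × √(p(1 − p)/n). At p = 0.80 and n = 20: 1.96 × √(0.16/20) = 1.96 × 0.0894 = 0.175. So a half-width under 20 points is reproduced at the green threshold.

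**2. The same formula at other rates, in percentage points.**

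| Observed rate | n = 20 | n = 60 |
|---|---|---|
| 80% | ±17.5 | ±10.1 |
| 75% | ±19.0 | ±11.0 |
| 70% | ±20.1 | ±11.6 |
| 60% | ±21.5 | ±12.4 |
| 50% | ±21.9 | ±12.7 |

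With n = 20 the limit is exceeded for every observed count from 6 to 14 (30% to 70%). That covers three of the four amber results (12, 13 and 14) and the red results nearest the boundary. For a half-width below 20 points, n must exceed 1.96² × p(1 − p)/0.20². At 60% this is 23.05, so 24; at 50% it is 24.01, so 25.

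**3. Does a just-green or just-red interval cross to the other colour?**

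| Result | Wald | Wilson | Exact (Clopper-Pearson) |
|---|---|---|---|
| 16/20 | 62.5–97.5% | 58.4–91.9% | 56.3–94.3% |
| 17/20, lower limit | 69.4% | 64.0% | 62.1% |
| 11/20, upper limit | 76.8% | 74.2% | 76.9% |

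At 16/20 the Wilson and exact intervals are asymmetric. They reach 21.6 and 23.7 points below the estimate, into red. The first green result that clears 60% by both is 17/20. No method takes a just-red 11/20 up to 80%.

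**4. Half-width by the other methods (half the interval's length).** Over observed rates of 50% to 80% at n = 20, Wilson runs from 20.1 down to 16.8 points and exact from 22.8 down to 19.0. So Wald separates red from green but misses the width. Wilson all but meets the width but does not separate 16/20 from red. Exact misses both in part.

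**5. Chance of misclassification under Table 2's own rule**, which uses the observed percentage. Binomial, n = 20:

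- Red called green: P(X ≥ 16) = 1.9% at a true 55%, 4.2% at 59% and 5.1% at the 60% boundary.
- Green called red: P(X ≤ 11) = 1.0% at a true 80%.

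**6. Pooled retention.** At 48/60 the exact interval is 67.7% to 89.2%, well clear of red.

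**The case against.** The strongest reply is that a symmetric ± figure is the form of a Wald interval and that, by Wald, the protocol's inference holds: every green count has a lower limit of 62.5% or more and every red count an upper limit of 76.8% or less. The widths above 20 points occur at amber and red results, and the excess is at most 1.9 points. The article also says only that there will be no *substantive* misclassification, and error rates of at most about 5% and 1%, taken at the boundaries, are compatible with that word. The second reason for the sample size, variance estimation, is untouched.

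Most of this stands, and it rules out three stronger readings.

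- A reader might infer that a just-green 16/20 reaches red whatever the method. It does not by Wald.
- A reader might infer that the statement about misclassification is false. The binomial figures do not clearly refute it.
- A reader might cite the 37% chance that a true 80% rate is rated below green. Almost all of that is amber (37.0% − 1.0% = 36.0%), and the article makes no claim about green against amber.

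The reply does not rescue the unqualified width. By the method that best supports the red/green inference, the half-width exceeds 20 points over the whole of 30% to 70%, and the text names completion explicitly. Nor is Wald a secure basis at n = 20, where its upper limit already passes 100% at 17/20 (85% + 15.65 points).

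**Conclusion.** The point holds as a correction to a stated figure. For SMART-arm completion, a 95% half-width under 20 points is met by Wald only at observed rates of about 75% or more, or 25% or less. Elsewhere it is missed by up to 1.9 points. The step from width to red/green separation holds by Wald and fails by Wilson and exact limits at one result, 16/20, by 1.6 and 3.7 points. Retention pooled over 60 is not affected.

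This rests on all 20 SMART participants forming the completion denominator and on retention being judged on all 60, which is the natural reading of Table 2. It does not show that 20 per arm is too few or that the progression rule misleads. Direct confusion of red and green is unlikely; the article supports that conclusion with a figure that does not establish it.

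**What to change.** In the Sample size section:

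- Replace the single limit with the Wald planning figures: about ±18 to ±22 points for SMART-arm completion rates of 50% to 80%, and about ±10 to ±13 points for rates pooled over 60.
- Name the interval to be used in reporting, Wilson or exact. Because these are asymmetric, give their limits at the threshold (16/20: 58.4% to 91.9% or 56.3% to 94.3%) and not only a ± figure.
- Support the statement on misclassification with the binomial probabilities: at most about 5% red-as-green at the 60% boundary and about 1% green-as-red at a true 80%.

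When results are reported, give the chosen interval beside each red/amber/green rating, so that a 16/20 is seen to be compatible with a rate just under 60%.

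The cost is a few sentences and a slightly less favourable stated precision. Sample size, thresholds and conduct do not change.
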